### Study design

The study was designed as a three-arm cluster-randomized controlled trial. Blinding of study participants or study staff to the intervention was not considered feasible or ethical. Ten of the 61 health facilities within the HDSS in Siaya County were purposively selected based on the following criteria: (1) high absolute malaria caseloads, (2) proximity of the facility to major roads for transport of supplies and samples, (3) government owned and run, and (4) minimum overlap with other known interventional/observational studies in the facility catchment; health facilities were chosen to maximize the distance between them, and all were at least 5 km from the next nearest health facility. All villages whose midpoint was located within 3 km of each health facility were included in the study. The villages surrounding each health facility were divided into three clusters along village boundaries such that the population was approximately evenly divided. One of the three clusters surrounding each health facility was randomly selected for the intervention, and the remaining two served as controls (Fig. 1). The purpose of the second control cluster was to allow the possible addition of a second intervention in the future. As no additional intervention arm was included in the study, for analysis purposes, the two control clusters were merged so that the study comprised 10 intervention and 10 control clusters with equal sample sizes. To reduce contamination between intervention and control clusters, the sampling frame for evaluations were limited to a core area within each cluster. The core area was defined as an area within the cluster that was ≥300 m from the perimeter of the cluster. The 300 m distance was chosen on the basis of previous studies at the site that indirectly demonstrated that the mass effect of a community based intervention (LLINs) extended to approximately 300 m based upon both entomologic [40] and epidemiologic [41] data. The area between the core and the perimeter of the cluster was defined as the buffer; though the intervention was performed in the buffer, data from individuals residing within the buffer area were not used for evaluations.

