The sample size was calculated, assuming a malaria prevalence of 40% in the control arm, a type I error rate of 5, and 80% power, to detect a relative difference in malaria prevalence of at least 50% between arms by study end. For ease of sampling, compounds were selected, and all individuals in the compounds were enrolled. A conservative coefficient of variation of 0.3 for between-cluster and—compound variance was used. Twenty compounds were selected per cluster for a total of 400 compounds across the study area (200 in each arm), and a total population of approximately 2000 individuals [45].

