### Data analysis

The primary outcome of incidence and prevalence analyses, in the cohort and cross-sectional studies, respectively, were microscopically confirmed *P. falciparum* parasitaemia. Arm-specific unadjusted prevalence ratios (PR) for parasitaemia and anaemia were calculated using data from the series of pre- and post-intervention cross-sectional surveys. These data were analyzed with a log-binomial model using generalized estimating equations to account for clustering. Pre- and post-intervention PRs between arms were evaluated using the same model. The incidence of clinical malaria, diagnostically confirmed by either RDT or microscopy, presenting to the MTaT study health facilities (passive surveillance) was calculated. Total case counts originating from each study arm at each health facility per month was divided by the total population of the study arm residing in the catchment area of the health facility according to the HDSS. The incidence of infection was determined from the cohort data. A Cox-Proportional Hazards model was used to compare time to infection between arms. Adjusted models were created to account for confounders including socioeconomic status, anti-malarial use, and LLIN use. Socioeconomic status (SES) was assessed using principal component analysis models of household assets [58]. Sporozoite and oocyst rates were compared by logistic regression using generalized estimating equations to account for correlated observations within the households. All analyses were performed using SAS statistical software version 9.3 (SAS Institute, Carey, NC).

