## Discussion

Previous results of trials or programmes incorporating mass campaigns, such as MTaT, for transmission reduction on a large-scale have been contradictory or inconclusive [31, 32]. As the population of individuals harbouring asymptomatic infections has been increasingly implicated in sustaining malaria transmission there has been renewed interest in evaluating time-limited MTaT in different transmission settings with high coverage of malaria control interventions for rapid malaria transmission reduction. The study site in western Kenya provided distinct advantages for evaluating MTaT including; (1) high malaria transmission despite high coverage with LLINs, (2) the existence of a HDSS through which sampling frames and population level data including births, deaths, and migration have been continuously monitored, (3) over 30 years of historical data on epidemiological and entomological malaria indices, (4) advanced laboratories and research infrastructure, and (5) strong relations with the communities and public and private health sectors in the region. In this manuscript, the strengths and limitations of the study design choices are discussed.

Interventions such as MTaT are designed to be effective at high coverage levels and, therefore, must be evaluated at the community level, but the cost and complexity of cluster-randomized trials combined with the heterogeneity of malaria transmission and differential access to health care complicate the design of such trials. To minimize differences in the spatial distribution of malaria transmission, differences in treatment availability and provider proficiency, the effect of distance on health-care seeking, and LLIN coverage, each cluster around the study health facilities was randomly assigned to the intervention or control arm, and only villages with a centroid within 3 kms from the health facilities were included. The result of this decision was that clusters abutted one another and were relatively small for campaign-style interventions, which are intended to be implemented over larger geographic spans for transmission reduction. This smaller size and geographic proximity may artificially increase the impact of migration as individuals may be more likely to migrate out of a smaller geographic cluster than a larger one, and through daily movement, may be more likely to enter a cluster that is closer to where they reside than one that is geographically distant.

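### The log-binomial GEE for prevalence and anaemia, as stated for 10 + 10 clusters, names neither the health-facility strata nor a small-sample method, so its 5% level is not secured in either direction

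*Protocol article*

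**What the plan says.** All references are to the protocol article.

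- **Model (Data analysis).** "Arm-specific unadjusted prevalence ratios (PR) for parasitaemia and anaemia were calculated", and "These data were analyzed with a log-binomial model using generalized estimating equations to account for clustering". The pre- and post-intervention contrast between arms uses the same model. The software is SAS 9.3. The section does not name the GEE unit, working correlation, variance estimator, type of test or degrees of freedom for this model, and it mentions no facility term.
- **Number of clusters (Study design).** After the two control clusters at each facility were merged, "the study comprised 10 intervention and 10 control clusters with equal sample sizes".
- **Allocation (Study design).** "One of the three clusters surrounding each health facility was randomly selected for the intervention". The 20 analysis clusters are therefore ten facility pairs.
- **Reason for allocating this way (Discussion).** "To minimize differences in the spatial distribution of malaria transmission, differences in treatment availability and provider proficiency", among other factors.
- **Error rate (Prevalence of malaria infection).** The survey was sized "assuming a malaria prevalence of 40% in the control arm, a type I error rate of 5, and 80% power". The target effect was a halving of prevalence. I read the error rate as 5% two-sided; the article does not state the sidedness.

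**The concern.** Two features of the design bear on the standard error of the prevalence ratio.

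The first is the small number of clusters. The sandwich variance is biased downwards when clusters are few, and the usual Wald test refers to the normal distribution. Both push the error rate above nominal.

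The second is the pairing by facility. If the two clusters of a facility resemble each other, as the design intends, an analysis that treats all 20 as unrelated overstates the variance of the arm contrast. That pushes the error rate below nominal and loses the precision that the within-facility allocation was meant to provide.

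The two errors work in opposite directions. How far they offset depends on the facility correlation, for which the article gives no figure. Prevalence of infection and of anaemia are both among the primary objectives, so the level of these tests and the coverage of the prevalence ratio intervals matter for the main claims.

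**Working it through.** **Inputs from the article.** Ten clusters per arm; control prevalence 40% against 20% under the target effect; coefficient of variation 0.3 between clusters and between compounds; about 2000 people, so about 100 per cluster (the table of evaluations gives 857 per arm, 85.7 per cluster).

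**Assumption.** The facility share ρ is the part of the between-cluster variance common to the two clusters of a facility. The documents do not give it; 0 to 0.75 is shown.

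**1. The plan's own figure.** The cluster-trial formula for proportions is c = a + (1.96 + 0.84)²[p0(1−p0)/m + p1(1−p1)/m + k²(p0² + p1²)]/(p0 − p1)², with a = 1 for unmatched and a = 2 for matched clusters. With c = 10:
- k = 0.3: 144 per arm unmatched, 176 matched.
- k² = 0.3² + 0.3² = 0.18: 405 unmatched, 839 matched.

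The last is 2.1% below 857 and is the only variant near it. This construction is inferred, not stated. If it is right, the survey was sized for matched pairs.

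**2. Twenty clusters as GEE units, no facility correlation.** With equal clusters the sandwich variance is too small by 9/10, so the size is about P(|t18| > 1.96 × √0.9) = P(|t18| > 1.859) = 7.9%. Simulation gave 7.7%, and direct log-binomial GEE fits (exchangeable, 1,200 runs) gave 8.0%.

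**3. Same test, facility correlation present but ignored.** At 40% prevalence the between-cluster variance is (0.3 × 0.4)² = 0.0144. The sampling variance is (0.24 − 0.0144)/100 = 0.00226. The total is 0.01666. The correlation between paired cluster prevalences is r = ρ × 0.0144/0.01666. The true variance of the arm contrast shrinks by (1 − r), but the estimated variance does not. The size is therefore roughly P(|t18| > 1.96 × √(0.9/(1 − r))).

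| ρ | r | critical value | approximation | simulation |
|---|---|---|---|---|
| 0 | 0 | 1.86 | 7.9% | 7.5–7.8% |
| 0.10 | 0.09 | 1.94 | 6.8% | 6.2–6.5% |
| 0.25 | 0.22 | 2.10 | 5.0% | 4.6–4.9% |
| 0.50 | 0.43 | 2.47 | 2.4% | 2.5–2.6% |
| 0.75 | 0.65 | 3.14 | 0.6% | 0.7–0.8% |

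The simulation ranges cover separate runs with 86 or 100 people per cluster.

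**4. Ten facilities as GEE units.** The pairing is now in the variance, but there are only ten units: P(|t9| > 1.96 × √0.9) = 9.6%. Simulation gives about 9% at every ρ tried.

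**5. Candidate repairs.**
- Variance × 10/9 with t18 and no facility term: 4.8% at ρ = 0, but about 2.7% at ρ = 0.25 and 1.3% at ρ = 0.50.
- Facility-paired analysis with 9 df: between about 4.4% and 5.0% at every ρ tried.

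**The case against.** The strongest objection is that the article is silent rather than wrong. It never says that an uncorrected Wald z test was used. Variance estimators and degrees of freedom are commonly left to a full protocol or analysis plan, which is not shown. This stands as a limit: the point can say that no correction and no facility term are named, not that none was applied. It does not remove the point, because the article does fix the model and the number of clusters, and the model as described suits neither the ten pairs nor their small number.

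A reader might infer that the test simply runs at about 8% and that the intervals are too narrow. The documents do not support that. The figure needs a Wald z test, the 20 clusters as units and no facility correlation. Allocation within facility was chosen to make the arms alike, so positive correlation is expected. From a share of about 0.25 upwards the size is at or below 5%.

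The type of test is also unstated. An uncorrected robust score test has a size of about 5.2% with 20 independent clusters, though this would not mend Wald intervals for the prevalence ratios.

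The calculation covers one between-arm contrast at one survey. No figure was derived for the pre/post model, although the same two features apply to it.

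Two extensions should not be made. The article mentions no robust variance for the Cox model. The mosquito GEE accounts for correlation within households, which is a separate question about the level of clustering.

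**Conclusion.** The concern holds in a conditional form. If the stated GEE is tested with an uncorrected sandwich Wald statistic, its size depends on the GEE unit and on an unknown facility correlation. It is about 8% with 20 unrelated clusters, about 9% with ten facility units, and about 2.5% with 20 clusters and an ignored facility share of 0.5. A size near 5% would arise only where two errors happen to cancel, at a share of about 0.25. The direction of the error in the intervals cannot be known from the article.

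These figures rest on equal cluster sizes, 40% prevalence, a coefficient of variation of 0.3 and a two-sided test. The facility share is assumed throughout. The point is worth acting on because it concerns primary objectives and is cheap to settle. It does not show that any reported result is wrong.

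**What to change.** State in Data analysis that the main comparison of parasitaemia and of anaemia respects facility and the small number of clusters, by one of two routes:

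- **Cluster level.** Take the log prevalence in the intervention cluster minus that in the merged control cluster at each facility, and make a paired t test on the ten differences (9 df). For the pre/post contrast, use the difference in change at each facility.
- **GEE.** Keep the log-binomial model with facility as the GEE unit, or with clusters as units and facility as a fixed effect (20 clusters − 10 facility terms − 1 arm term = 9 df). Use a bias-corrected sandwich variance (Kauermann-Carroll or Mancl-DeRouen) and a t reference on about 9 df.

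Name the GEE unit and the variance estimator explicitly. Do not add an 18-df correction without a facility term; that would make the test more conservative if facility correlation is present.

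The cost is a program option or a short cluster-level analysis, with no new data. Intervals become wider than those of an uncorrected facility-level GEE by about √(10/9) × 2.26/1.96 = 1.054 × 1.154 = 1.22, or 22%. Compared with a 20-cluster analysis that ignores facility, they may be wider or narrower, depending on the facility correlation.

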### Measurement of malaria transmission outcomes

Four separate strategies were used to evaluate outcomes related to malaria transmission: (1) annual population-based cross-sectional studies for malaria prevalence, (2) active surveillance for malaria infection utilizing a longitudinal cohort, (3) passive surveillance of laboratory-confirmed clinical malaria cases in study health facilities, and (4) entomological transmission indices. Eligible participants residing within a household located within the core area were included in the sampling frame for study evaluations and analyses. Inclusion criteria, sample sizes, and main malaria transmission outcomes for each of the evaluations can be found in Table 1.

**Table 1 Tab1:** Inclusion criteria, sample size, and main outcome by evaluation type

Evaluation type	Inclusion criteria	Sample size	Main outcome
Cross-sectional studies	≥1 month of age	857 per arm	Community malaria prevalence
Longitudinal cohort study	≥1 year of age, not pregnant at time of recruitment	330 per arm	Incidence of malaria infection
Passive surveillance	Living within the core area of a cluster	N/A	Incidence of clinical malaria
Entomological surveillance	Household in either a control or intervention cluster	120 control and 60 intervention households per month	Monthly *P. falciparum* oocyst and sporozoite rates, *Anopheles* parity rate

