#### Incidence of clinical malaria

The incidence of clinical malaria from passive surveillance between residents of intervention and control clusters was compared. All persons registered with the HDSS and living within the core areas of clusters were considered under surveillance. Patients attending one of the 10 study health facilities were interviewed by study staff, who used laptop computers to determine if the patient was registered with the HDSS and lived in the study area. Patients not registered with the HDSS, but meeting criteria for HDSS registration [34] were asked for consent to participate, and their data were included in the study. For eligible patients, study staff recorded data from the clinical register into laptop computers, including history of fever/suspected malaria, malaria confirmatory testing and results, and medications prescribed. Per national guidelines, all patients presenting to a health facility with history of, or current fever, were considered suspected clinical malaria cases, were diagnosed by either RDT or blood smear microscopy, and were treated according to Kenya Ministry of Health Guidelines [44]. Data were retrieved from each of the 10 health facilities on a weekly basis.

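### The clinical malaria rate, as written, divides core-area cases (some not registered in the HDSS) by the study arm's total HDSS population in the catchment

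*Protocol article*

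**What the plan says.** Incidence of clinical malaria falls within the first specific primary objective (*Study objectives*). The article defines the quantities behind it in several places.

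- **Who is under surveillance.** *Incidence of clinical malaria*: "All persons registered with the HDSS and living within the core areas of clusters were considered under surveillance". Table 1 gives the inclusion criterion as "Living within the core area of a cluster", and Table 2 agrees.
- **Buffer residents.** *Study design* defines the core as the part of a cluster at least 300 m inside its perimeter and adds that "data from individuals residing within the buffer area were not used for evaluations".
- **Unregistered patients.** Attenders outside the HDSS register who would qualify for registration were "asked for consent to participate, and their data were included in the study" (*Incidence of clinical malaria*).
- **The rate.** *Data analysis* takes "Total case counts originating from each study arm at each health facility per month", "divided by the total population of the study arm residing in the catchment area of the health facility according to the HDSS". This is the only place where the denominator is defined.

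**The concern.** A rate needs the same people above and below the line. Here the two can differ in two ways. First, cases are confined to the core, but the stated population is the arm's total in the catchment, which on its plain wording includes the 300 m buffer. Second, unregistered patients can be cases but are not in a population taken from the HDSS until a census round enumerates them.

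The level of clinical malaria incidence is directly at stake. The between-arm comparison is at stake only if the mismatch is unequal across arms. The design leaves that open: each facility has one intervention cluster and two control clusters, the controls were merged for analysis, and the article does not say whether the control core was drawn before or after merging. A merged block has proportionally less perimeter, and so a larger core share, than a single third.

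**Working it through.** The article states no rate, core population or number of unregistered patients, and Table 1 gives N/A as the passive-surveillance sample size. There is therefore no planned figure to reproduce. What can be derived is how each mismatch changes the rate and the ratio.

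**Inputs from the article:** buffer 300 m; villages included if their midpoint lies within 3 km of the facility; one intervention and two control clusters per facility, with the controls merged (all *Study design*).

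**Inputs assumed:** *f*, the core share of an arm's population, and *s*, the unregistered share of an arm's cases. To illustrate *f*: a 3 km disc with even population, cut into three 120-degree sectors, with a 300 m strip removed inside each perimeter (simulation, 2,000,000 points). This gives *f* = 0.644 for a 120-degree sector and 0.722 for a merged 240-degree block.

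**Formulas** (I = intervention, C = control):

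- Reported rate = rate in registered core residents × *f* / (1 − *s*).
- Ratio factor from the core mismatch = *f*_I / *f*_C.
- Ratio factor from unregistered patients = (1 − *s*_C) / (1 − *s*_I).

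**Effect on levels**

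- Whole-arm denominator, *f* = 0.644, *s* = 0: the rate is reported at 64% of its value, 36% too low. At *f* = 0.722 it is 28% too low.
- Core-only denominator (*f* = 1): *s* = 0.05 inflates the rate by 1/0.95 = 1.05, and *s* = 0.10 by 1/0.90 = 1.11.
- Both together, *f* = 0.644 and *s* = 0.10: 0.644/0.90 = 0.72. The errors offset in part and do not cancel.

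**Effect on the arm ratio**

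| Assumption | Calculation | Factor |
|---|---|---|
| Cores drawn per original third | 0.644/0.644 | 1.00 |
| Control core redrawn after merging | 0.644/0.722 | 0.89 |
| Core shares 0.50 (I), 0.60 (C) | 0.50/0.60 | 0.83 |
| Core shares 0.60 (I), 0.50 (C) | 0.60/0.50 | 1.20 |
| Unregistered shares equal (5% or 10%) | 0.95/0.95 or 0.90/0.90 | 1.00 |
| Unregistered 5% (I), 10% (C) | 0.90/0.95 | 0.95 |
| Unregistered 10% (I), 5% (C) | 0.95/0.90 | 1.06 |

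With a factor of 0.89, a true ratio of 1.00 would appear as 0.89, and 0.70 as 0.70 × 0.892 = 0.62.

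**Facility attended versus residence.** Cases are tabulated by the facility where they present, and population by the catchment where people live. A core resident of one catchment who attends another study facility is counted at the second facility and is in the denominator of the first. Because cases are assigned to the arm they come from, summing over the ten facilities puts that person once in the right arm's cases and once in the right arm's population. Facility-level rates can shift; overall arm totals do not.

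**The case against.** The best defence is that a core-only denominator was intended. *Measurement of malaria transmission outcomes* says: "Eligible participants residing within a household located within the core area were included in the sampling frame for study evaluations and analyses". *Data analysis* uses the same unit, the study arm, for cases and for population, and repeats the core limit for neither. It can seem selective to import the limit into one and not the other. This has force: a core-only reading is possible, and the buffer mismatch follows from the literal wording rather than from any evidence of what was computed. But the sentence quoted concerns eligible participants and the sampling frame, whereas the one sentence that defines the denominator says total population. Two analysts could build different rates from this text.

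The core-only reading does not cure the second mismatch. Those added were "but meeting criteria for HDSS registration [34] were asked for consent to participate, and their data were included in the study", so they can be cases before they are in the register. The census runs three times a year (*Study area and population*), so the gap may be temporary for each person, and the number may be small. The article gives no reason to expect it to differ by arm.

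A reader might go further and infer three things that the documents do not support:

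- **That the denominator is everyone in the facility catchment.** It is not; it is specific to the study arm.
- **That the trial would show a spurious 11% reduction favouring MTaT.** That needs a whole-arm denominator, a control core redrawn on the merged perimeter, a perfect disc and an even population. The article establishes none of these, and clusters in fact followed village boundaries.
- **That cross-attendance biases the arm comparison.** It does not shift the overall arm totals, as shown above.

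**Conclusion.** Wrong as written. Core-restricted cases, with unregistered patients added, are divided by the study arm's total HDSS population in the catchment. Taken literally, incidence levels are wrong: too low through buffer residents in the denominator, too high through unregistered patients in the numerator alone. If a core-only denominator was meant, the first error disappears and the second remains.

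Bias in the arm ratio is conditional on unequal core or unregistered shares. The illustrative factors run from 0.83 to 1.20 for unequal core shares and from 0.95 to 1.06 for unequal unregistered shares, and are exactly 1.00 when shares are equal. Every share used is an assumption, so these figures show sensitivity and do not estimate what happened. Similarly, the article plans a cost-effectiveness evaluation (*Costing*) but does not say that it uses these rates, so no error there can be asserted. The point still merits correction because it concerns a stated rule for an outcome under a primary objective, and correcting it is cheap.

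**What to change.** Amend the passive-surveillance rule in *Data analysis*:

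1. Define the denominator as HDSS person-time of core-area residents, by arm and cluster of residence.
2. Count a case if the patient lives in that core, whichever study facility was attended, so that facility-level rates also match.
3. Either exclude unregistered patients from the primary rate or add them to the person-time. Report a sensitivity analysis done the other way.
4. State whether the control cores were drawn before or after the two control clusters were merged.

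With the same people in numerator and denominator, both distortion factors become 1.00. The cost is a different HDSS extract and revised wording, with no new data collection, since compounds are already mapped and residence updated at each census round. If unregistered patients are excluded, a few cases may be lost.

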The sample size for the cohort study was based on detecting a relative difference in the incidence of malaria infection of at least 30% between the intervention and control arms over two years of follow-up. Based on data from previous studies, a baseline of 1.6 malaria infections per person per year, and a coefficient of variation of 0.25 were estimated for this study. A type I error rate of 5 and 80% power were used resulting in a sample size of 330 individuals per arm for a total sample size of 660 [45].

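### The cohort Cox comparison is described with no allowance for the randomised clusters; with ordinary standard errors its 5% test would run at about 22–25% at the plan's own CV of 0.25

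*Protocol article*

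**What the plan says.** Under Study design, the villages around each of ten health facilities form three clusters. One is randomised to the intervention, and the two controls are merged for analysis, giving 10 against 10. Under Incidence of malaria infection, 33 people are drawn from each of the 20 clusters, 330 per arm. Incidence of infection belongs to the first primary objective.

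The cohort sample size rests on "detecting a relative difference in the incidence of malaria infection of at least 30" per cent over two years and a control rate of 1.6 infections per person-year. It adds that "a coefficient of variation of 0.25 were estimated for this study" and concludes: "A type I error rate of 5 and 80% power were used resulting in a sample size of 330 individuals per arm".

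The Data analysis section then treats three outcomes differently:

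- Prevalence: "These data were analyzed with a log-binomial model using generalized estimating equations to account for clustering".
- Sporozoite and oocyst rates: "generalized estimating equations to account for correlated observations within the households".
- Cohort incidence: "A Cox-Proportional Hazards model was used to compare time to infection between arms", followed by "Adjusted models were created to account for confounders including socioeconomic status, anti-malarial use, and LLIN use".

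For the cohort it mentions no robust variance, frailty, facility stratification or cluster-level summary.

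**The concern.** A Cox model named without qualification has model-based standard errors, which treat the 660 people as independent. Only 20 analysis clusters carry the treatment contrast, and the plan's own CV says that their infection rates differ by more than chance among individuals. An analysis that omits this variation would read part of the ordinary difference between villages as an effect of mass testing and treatment. The confidence interval would be too narrow and the false-positive rate above 5%. The sample size counts this variance and the analysis, as described, does not, so the two do not match.

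**Working it through.** **Inputs from the article.** Rates of 1.6 and 0.7 × 1.6 = 1.12 per person-year; CV k = 0.25; 10 clusters per arm of 33; two years; 5% error (taken as two-sided) and 80% power. The cohort paragraph does not say what the CV is between; I read it as between clusters, and step 1 supports that.

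**1. Reproduce the sample size.** The cluster-trial formula for rates is c = (1.96 + 0.84)² × [(λ0 + λ1)/y + k²(λ0² + λ1²)] / (λ0 − λ1)², with y = 33 × 2 = 66 person-years per cluster.

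- (1.6 + 1.12)/66 = 0.0412
- 0.0625 × (2.56 + 1.2544) = 0.2384
- c = 7.85 × 0.2796 / 0.2304 = 9.53, so 10 clusters per arm; power with 10 is 81.9%.

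Adding one cluster as a small-sample term gives 10.53, and power with 10 falls to 77.7%. The match is on clusters and power, not exactly on 330 people, but it shows that the design counted between-cluster variance.

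**2. Standard error of log HR, first infection, two years.**

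- Expected first infections: D = 660 × (1 − e^(−3.2)) ≈ 633.
- Ordinary variance: 4/633 = 0.0063, SE 0.080.
- Between-cluster part: 2 × ln(1 + 0.25²)/10 = 2 × 0.0606/10 = 0.0121.
- Total: 0.0184, SE 0.136.
- Ratio: 0.136/0.080 ≈ 1.71. About two thirds of the variance (0.0121/0.0184) is left out.

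**3. Real error of the nominal 5% test.** 2 × [1 − Φ(1.96/1.71)] ≈ 25.1%.

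**4. Shorter follow-up.** Recruitment is described at each cross-sectional survey, so one year per person is possible. Then D ≈ 527, the SE ratio is 1.61 and the error 22.4%.

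**5. Simulation.** Under no effect, with gamma-distributed cluster rates, 20 clusters of 33, monthly visits and Efron's method for ties (1,500 runs per setting), the error was 25.7% over two years and 22.1% over one. With no clustering it was 5.7–6.2%. Breslow's method for ties shrinks the estimate when ties are heavy, so it would lower these figures somewhat.

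**6. Conditions that reduce the inflation (two years).**

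| Condition | Error |
|---|---|
| 25% of between-cluster variance shared within facility (assumed) | 21% |
| 50% shared (assumed) | 16% |
| 75% shared (assumed) | 11% |
| Controls counted as 20 separate clusters, CV 0.25 | 21% |
| Effective CV 0.15 (assumed) | 13% |
| Effective CV 0.10 (assumed) | 9% |

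The sharing rows multiply 0.0121 by the unshared fraction. For 50%, 0.0063 + 0.0061 = 0.0124, the ratio is 1.40 and the error 16%. For 20 control clusters the between part is 0.0606/10 + 0.0606/20 = 0.0091. At CV 0.10 it is 0.0020 and the SE ratio 1.15.

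**The case against.** The best defence is that this is a condensed article that gives the Cox comparison one sentence. The investigators plainly planned for clustering: it is in the cohort sample size and in the prevalence model. The variance estimator is a detail that the full plan may hold, and a robust or frailty method may have been used and not reported. The mosquito analysis is also a weak contrast, because its correlation is at household level, not at the randomised cluster.

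A second objection concerns size. Randomisation was within facility, to balance local transmission and access to care, and variation common to a facility cancels between arms. The figure for independent clusters is then an upper value for the first-infection analysis.

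Both points stand in part. The first makes the conclusion conditional. It does not remove the point, because the same paragraph is specific about correlation for two other models and about covariates for the adjusted ones; someone following it as written would fit a Cox model with the wrong standard error. The second widens the range downwards, but even with 75% of the variance shared the error is about twice the nominal level.

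**Conclusion.** The point holds in conditional form. As described, a primary comparison in a cluster-randomised trial makes no allowance for the randomised unit. With ordinary standard errors its real type I error would be about 22–25% at the documented CV if clusters vary independently. The 11–21% and 9% figures rest on assumed facility sharing and an assumed CV; the article gives neither.

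Three stronger readings are tempting and not supported:

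- A reader might infer that clustering was in fact ignored, or that the trial's reported test is wrong. The text is silent on this; it does not say so.
- A reader might call the standard error far too small whatever the CV. That fits CV 0.25, not CV 0.10, where the ratio is 1.15.
- A reader might add repeat infections, which would worsen the inflation. The article speaks only of time to infection, so I attach no figure to that case.

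**What to change.** State that the cohort comparison uses variance at the level of the randomised cluster, and say how. Two options:

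- **Cox model with robust variance aggregated on cluster**, with a t reference and a small-sample correction for 20 clusters. If the model is also stratified by facility, aggregate on facility instead. With one cluster per arm in a balanced stratum, each cluster carries half of the stratum's score, so summing squares by cluster gives (1/2)² + (1/2)² = 1/2 of the right variance. The SE would be too small by √2, and the error would return to 2 × [1 − Φ(1.96/1.41)] ≈ 17%.
- **Cluster incidence rates compared within facility**, as ten paired differences in log rate with a t reference on 9 degrees of freedom.

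If such a method was already used, one sentence settles the matter. If not, the comparison must be refitted. No new data are needed. The cost is a wider confidence interval, of the order of 1.7 times at CV 0.25 with independent clusters and less if facilities share variation, plus the somewhat larger t quantile.
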